| **Study design** | This study is a prospective observational cohort study actively monitoring the hematologic response, safety and tolerability of routine treatment of *P. falciparum, P. vivax* and mixed malaria infections (*P. falciparum + P. vivax*). The study will be conducted in Alikadam in the Chittagong Hill Tracts (CHT). |
| **Duration of administration** | - *P. falciparum*: supervised AL for 3 days + single dose PQ - *P. vivax*: Supervised CQ for 3 days + unsupervised PQ for 14 days - Mixed infections: supervised AL for 3 days + unsupervised PQ for 14 days |
| **Duration of patient enrolment** | - Six months |
| **Endpoints** | Safety Endpoints:   - Proportion of patients with severe anaemia (Hb<7g/dl) - Proportion of patients receiving blood transfusion - Fractional change in Hb between baseline and day 9,16, 23 and 30 (incl. proportion of patients with >25% drop in Hb between the timepoints) - Proportion of patients with anaemia less than 8g/dl on day 3 and day 9 - Proportion of patients with adverse and serious adverse events   Efficacy endpoints:   - Proportion of patients with any parasitemia on day 1, 2 and 3 after treatment - Proportion of patients with fever on day 1, 2 and 3 after treatment - Recurrence of parasitaemia within 30 days of follow up   Other Endpoints:   - Proportion of patients adhering to 14 days of primaquine treatment in the vivax cohort as measured by Masimo and pill count - Distribution of G6PD activity among the study population - Frequency and type of variants of the G6PD gene within the study population |
| **Date of first patient enrolled** |  |

Contents

[1. Background 5](#_Toc395861878)

[1.1. Local malaria epidemiology and treatment guidelines 5](#_Toc395861879)

[1.2. Study Site 7](#_Toc395861880)

[**1.3.** **Context of project** 9](#_Toc395861881)

[2. Rationale and Aim 9](#_Toc395861882)

[3. Objective 9](#_Toc395861883)

[4. Methods 10](#_Toc395861884)

[4.1. Study Design 10](#_Toc395861885)

[4.2. Inclusion Criteria 10](#_Toc395861886)

[4.3. Exclusion Criteria 10](#_Toc395861887)

[4.4. Study Procedures 11](#_Toc395861888)

[4.4.1. Treatment & sample collection 11](#_Toc395861889)

[4.4.2. Concomitant treatment 15](#_Toc395861890)

[4.4.3. Rescue treatment 15](#_Toc395861891)

[4.4.4. Loss to follow up 15](#_Toc395861892)

[4.4.5. Patient withdrawal and protocol violation 15](#_Toc395861893)

[4.5. Laboratory and test procedures 16](#_Toc395861894)

[4.5.1. Microscopy 16](#_Toc395861895)

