### Treatment & sample collection

Patients will receive the following treatment according to national guidelines (Annex II, IV and V) and will be asked to return for follow up:

- **Vivax patients**

CQ (Annex IV) will be administered for three days under direct observation. All patients will be observed for 30 min after drug administration for adverse reactions or vomiting. Any patient who vomits during this observational period will be re-treated with the same dose and observed for an additional 30 min. If the patient vomits the study drug a second time, he or she will receive rescue therapy as defined by the national treatment guidelines (Annex VI).

PQ (Annex V) will be administered unsupervised for 14 days from day 3 – 16.The complete treatment course of PQ will be provided to the patients after completion of schizontocidal treatment. All patients will receive instructions on how to take the drugs and will be asked to return for follow up on, day 6, day 9, day 12, day 16 (at the end of treatment), day 23 and day 30, as well as whenever the patients suffers from signs and symptoms consistent with malaria or an adverse reaction to one of the study drugs. (Annex IX).

- **Falciparum patients:**

AL will be administered twice daily for three days (Annex III). The morning dose will be supervised and the patients given tablets for the evening dose. Whenever supervised treatment is administered, the study patients will be observed for 30 min after drug administration for adverse reactions or vomiting. Any patient who vomits during this observational period will be re-treated with the same dose of medicine and observed for an additional 30 min. If the patient vomits the study drug a second time, he or she will receive rescue therapy (Annex VI). PQ will be given to the patients after schizontocidal treatment is finished and the patients are advised to take the single dose (Annex V) on day 3 unsupervised. All patients will be asked to return for follow up on day 9, day 16, day 23, day 30 and whenever participants suffer from signs and symptoms consistent with malaria or an adverse reaction to one of the study drugs within the follow up period (Annex IX).

- **Patients with mixed infection (Pf and PV):**

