**Table: Treatment, follow up and sample collection schedule *P.f*, *P. vivax* and mixed infections:**

| **Vivax Patients & Patients with mixed infection** | Day 0 | Day 1 | Day 2 | Day 3 | Day 4 | Day 5 | Day 6 | Day 7 | Day 8 | Day 9 | Day 10 | Day 11 | Day 12 | Day 13 | Day 14 | Day 15 | Day 16 | Day 23 | Day 30 | Un-scheduled visit |
| --- | --- | --- | --- | --- | --- | --- | --- | --- | --- | --- | --- | --- | --- | --- | --- | --- | --- | --- | --- | --- |
| FU P.f. patients | X | X | X | (x) |  |  |  |  |  |  |  |  | X |  |  |  | X | X | X |  |
| FU P.v. patients & mixed | X | X | X | (x) |  |  | X |  |  | X |  |  | X |  |  |  | X | X | X |  |
| Consent | X |  | X |  |  |  |  |  |  |  |  |  |  |  |  |  |  |  |  |  |
| Urinary Pregnancy testing (females, 13- 49years) | X |  |  |  |  |  |  |  |  |  |  |  |  |  |  |  |  |  |  |  |
| Capillary Finger Prick | X | X | X |  |  |  |  |  |  | X |  |  |  |  |  |  | X | X | X | X |
| Venous Blood Sample | X |  |  |  |  |  |  |  |  |  |  |  |  |  |  |  |  |  |  | X* |
| Microscopy | X | X | X | (X) |  |  | X |  |  | X |  |  | X |  |  |  | X | X | X | X |
| Hb | X | X | X | (X) |  |  | X |  |  | X |  |  | X |  |  |  | X | X** | X** | X |
| ACT treatment Pf and Pf/Pv | X | X | X |  |  |  |  |  |  |  |  |  |  |  |  |  |  |  |  |  |
| PQ treatment Pf |  |  |  | X |  |  |  |  |  |  |  |  |  |  |  |  |  |  |  |  |
| CQ treatment Pv | X | X | X |  |  |  |  |  |  |  |  |  |  |  |  |  |  |  |  |  |
| PQ treatment Pf and Pf/Pv |  |  |  | X | X | X | X | X | X | X | X | X | X | X | X | X | X |  |  |  |
| Masimo*** |  |  |  |  |  |  |  |  |  |  |  |  |  |  |  |  | X** |  |  | X |
| Pill count |  |  |  |  |  |  |  |  |  |  |  |  |  |  |  |  | X** |  |  |  |
| AE monitoring  *in case of recurrent parasitaemia  ** in Pv and Pf/Pv patients only  ***only in adults and children >2 yearsX | X | X | X |  |  |  |  |  |  | X |  |  |  |  |  |  | X | X | X | X |

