## Hemoglobin

. Haemoglobin (Hb) will also be measured at baseline and on all follow up visits using a Hemocue Hb (Angelholm, Sweden) machine.

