# Assessment of variables and statistical methodology

## Safety endpoints

- Proportion of patients with severe anaemia (Hb<7g/dl)
- Proportion of patients receiving blood transfusion
- Fractional change in Hb between baseline and day 6, 9,12,16, 23 and 30 (incl. proportion of patients with >25% drop in Hb between the timepoints)
- Proportion of patients with anaemia less than 7g/dl on day 3 and day 9
- Proportion of patients with adverse and serious adverse events

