# Statistical analyses

- Safety data will be presented as summary statistics (including number, mean, median, interquartile range, standard deviation, minimum and maximum) of all vital signs variables (values and changes from baseline) will be calculated for each visit by treatment group.
- G6PD activity will be categorised and the relative risk (RR) of a drop of Hb > 25% between day 3 and 9 and day 3 and 16 and day 23 and 30 will be calculated per category for all participants treated with 14 days of PQ.
- Hematological results will be presented as continuous variable of Hb concentration at Day 0, 3, 6, 9, 12 and 16. The fractional fall in Hb between baseline and day 9 and 16, will be calculated, as well as the proportion of patients with anaemia less than 7g/dl between day 3 and day 9.
- Parasite clearance rate will be defined according to the World Wide Antimalarial Resistance Network guidelines (WWARN)[[20](#_ENREF_20)]. The parasite clearance time (PCT) is defined as the time elapsed between the patient’s first dose and the time of the first negative blood slide.
- G6PD variants detected will be presented descriptively, G6PD activity observed will be displayed in the form of a histogram displaying G6PD activity vs. number of patients.

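### The fractional Hb change endpoint is defined on three different sets of days, and the passages on when Hb is taken in falciparum patients contradict each other

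*Protocol*

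**What the plan says.** **Endpoint days.** The Synopsis (Endpoints) lists "Fractional change in Hb between baseline and day 9,16, 23 and 30". Section 5.1, Safety endpoints, lists "Fractional change in Hb between baseline and day 6, 9,12,16, 23 and 30". Both attach to their list the proportion of patients with a drop of more than 25% between the timepoints. Section 7, Statistical analyses, says "The fractional fall in Hb between baseline and day 9 and 16, will be calculated". The same bullet of Section 7 also presents Hb concentration on days 0, 3, 6, 9, 12 and 16.

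**The >25% drop.** For patients on 14 days of primaquine, Section 7 computes the relative risk by G6PD category of "a drop of Hb > 25% between day 3 and 9 and day 3 and 16 and day 23 and 30".

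**Collection.** The Hemoglobin section says "Haemoglobin (Hb) will also be measured at baseline and on all follow up visits". In the schedule table the Hb entries for days 23 and 30 carry a footnote, "in Pv and Pf/Pv patients only". For falciparum patients, Treatment & sample collection says "All patients will be asked to return for follow up on day 9, day 16, day 23, day 30", but the falciparum visit row of the schedule marks days 0, 1, 2, (3), 12, 16, 23 and 30, with no day 9. The case record form (Annex IX) has Hb fields on days 23 and 30 with no species restriction.

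**The concern.** The primary objective is to assess side effects of unsupervised primaquine, and the Background names haemolysis as the hazard. The fractional Hb change and the >25% proportion are among the five safety endpoints that address it. If three current sections give three day lists, two analysts working from the same data can report different falls and different >25% proportions, and both can claim to follow the protocol. The list could then be chosen after the data are seen.

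The collection conflict is of another kind. A later analysis plan can choose among day lists, but it cannot recover Hb values that a site did not take because it followed the schedule.

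**Working it through.** No sample-size or power figure is involved, so there is nothing of the plan's to reproduce. The check compares the day lists as sets and intersects them with the days on which Hb is taken.

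**1. The three lists.**
- Synopsis: {9, 16, 23, 30}
- Section 5.1: {6, 9, 12, 16, 23, 30}
- Section 7: {9, 16}

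Section 7 names 2 of the 6 days in 5.1. Primaquine for vivax and mixed infection runs from day 3 to day 16. After day 3, the schedule's Hb row has days 6, 9, 12 and 16 in that window, so Section 7 uses 2 of 4. Study Procedures says the day 6 and day 12 visits were added for these patients to make sure the treatment is safe.

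**2. Which days can be filled.** For vivax/mixed, Hb is scheduled on all six days, so every list can be filled. For falciparum the answer depends on which passages are combined:

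| Falciparum visits from | Hb rule from | Hb days | Synopsis | 5.1 | Section 7 |
|---|---|---|---|---|---|
| Text (9, 16, 23, 30) | Hemoglobin section | 9, 16, 23, 30 | 9, 16, 23, 30 | 9, 16, 23, 30 | 9, 16 |
| Text | Schedule footnote | 9, 16 | 9, 16 | 9, 16 | 9, 16 |
| Schedule row (12, 16, 23, 30) | Hemoglobin section | 12, 16, 23, 30 | 16, 23, 30 | 12, 16, 23, 30 | 16 |
| Schedule row | Schedule footnote | 12, 16 | 16 | 12, 16 | 16 |

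Day 16 is the only day common to every cell. Day 9 is in all three lists but drops out if the schedule's visit row is followed. Day 6 is not a falciparum visit under any passage, so the 5.1 list cannot be filled for that group.

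**3. Direction.** {9, 16} is a subset of both other lists. For any patient, the largest fall over {9, 16} therefore cannot exceed the largest fall over the 5.1 list. It is smaller whenever the lowest listed value falls on another day, such as day 6 or 12.

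**4. Size, as an illustration only.** The document gives no expected nadir day, depth or recovery time. A simulation assumed one dip per patient from day 2, depth mean 18% and SD 10%, nadir uniform over days 5-8, 8-13 or 5-16, linear recovery over 10, 14 or 20 days, and no measurement error. About 24% of patients then truly fall by more than 25%.
- The 5.1 list shows 16.1% to 20.6% of patients with such a fall on at least one listed day.
- The Section 7 list shows 7.0% to 15.6%. The Synopsis list gives the same figures, so days 23 and 30 add nothing under these assumptions.
- Within the same scenario the gap runs from 19.9 − 15.6 = 4.3 points to 16.1 − 7.0 = 9.1 points. In about 50 vivax patients that is 50 × 0.043 = 2.2 to 50 × 0.091 = 4.6 patients.

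**5. The >25% intervals.** The endpoint text measures from baseline. It does not define baseline, though the case record form puts that label on the day 0 Hb. Section 7 starts two intervals on day 3 and the third on day 23, which is 23 − 16 = 7 days after the last primaquine day. A fall between day 0 and day 3, before primaquine, counts from baseline but not from day 3. The case record form passes from day 2 to day 6 with no day 3 page, and day 3 is in brackets in the schedule.

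**6. A related mismatch.** The schedule's finger-prick row has no mark on days 6 and 12, although its Hb row does, and the case record form makes the Hb field conditional on a finger prick.

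**The case against.** The strongest reply is that these are per-visit descriptive summaries, that a separate analysis plan may settle which days are tabulated, and that any fixed visit list can miss a nadir. A fall reported at days 9 and 16 is not biased for those days. All this is fair as far as it goes. It does not remove the contradiction, because the protocol does not leave the days open: it fixes them three times, differently.

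Four stronger readings are tempting, and the document does not support them.

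- **That the day 6 and 12 Hb values go unused.** They do not. Section 7 presents Hb concentration on those days; only the fractional fall is not named for them.
- **That the day 9 and 16 fall feeds the >25% relative risk.** It does not. That analysis has its own intervals. It is the Synopsis and 5.1 that tie the >25% proportion to their day lists.
- **That falciparum patients will have no Hb on days 23 and 30.** This is an unresolved conflict. The text brings them back on both days, Study Procedures has a finger prick at every follow-up, and the Hemoglobin section measures Hb at every visit. The case record form points the same way, since it limits methaemoglobin by species but not Hb. It is weak evidence, because its day 6 Hb field is also unrestricted although falciparum patients have no day 6 visit.
- **That haemolysis is understated by a known amount, in the main haematological endpoint.** The direction in step 3 is a matter of logic, but the size rests wholly on assumed values, and the protocol does not rank its five safety endpoints.

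**Conclusion.** The point holds as a contradiction within the current text. One endpoint has three incompatible day lists, and the >25% drop is defined from baseline in two places but analysed over different intervals in a third. The schedule disagrees with the text on falciparum Hb at days 23 and 30 and on whether the falciparum visit is on day 9 or day 12.

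Two consequences follow. The Section 7 list can miss a vivax or mixed patient's lowest value during the primaquine course; how often is not known from the document, and the 2 to 5 patients in 50 above is an illustration under assumed nadir and recovery. A site that follows the schedule will have no day 23 or day 30 Hb in the approximately 160 falciparum patients targeted in Sample Size, which no later analysis can repair. Whether that happens depends on which passage the site follows. The text should be corrected; the design does not fail because of it.

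**What to change.** - **One day list per species group**, identical in the Synopsis, Section 5.1 and Section 7. For vivax/mixed, use the full 5.1 list (6, 9, 12, 16, 23, 30), since Hb is already scheduled on those days.
- **One defined baseline**, with the >25% proportion and its relative risk derived from the same timepoints. If a day 3 starting value is wanted as well, define it separately and provide for it on the case record form.
- **Reconcile the schedule's Hb footnote, falciparum visit row and finger-prick row** with Study Procedures, Treatment & sample collection, Hemoglobin and Annex IX. Which passage is right is for the investigators to settle. Alternatively, limit the falciparum endpoint to the days on which Hb is in fact taken in that group.
- **A maximum fall across visits** may be added as a descriptive summary within a species group. It would be a new quantity and should not be compared between groups with different numbers of readings. With independent measurement error and no true change, its expected value is about 1.27 SD over six readings and 0.56 SD over two, a gap of 0.71 SD from the count alone.

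Cost: for vivax/mixed, wording only. For falciparum, either Hb at two visits that are already scheduled or the loss of two endpoint days.

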**Secondary:**

- To assess the schizontocidal efficacy of 3 days chloroquine (CQ) for *P. vivax*
- To assess parasite clearance rates in P*. falciparum* patients treated with artemether-lumefantrine (AL)
- To determine the risk of haemolysis associated with G6PD activity
- To determine the distribution of G6PD activity and genetic variants among malaria patients
- To determine parasite related factors that may affect treatment outcome

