# Laboratory and test procedures

## Microscopy

Slides for microscopy will be collected upon enrolment and on all follow up days as well as on any unscheduled visit days.

All slides collected between day 0 and day3 will be re-read by an expert microscopists. Blood smears with discordant results (differences between the two microscopists regarding species diagnosis, parasite density of > 50% or regarding the positivity in general) will be re-examined by a third, independent microscopist, and parasite density will be calculated by averaging the two closest counts.

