**Annex IX**

**Case record form**

**Date of Birth:** **OR** **Age:** ☐☐ in ☐ Month ☐ Year

D

D

M

M

Y

Y

Y

Y

**Sex:** ☐ Male ☐ Female **Ethnicity:** ☐ Tribal ☐ Non Tribal

**If tribal**, which tribe? ☐ Marma ☐ Chakma ☐ Tripura ☐ Tanchangya ☐ Khyang ☐ Bawm ☐ Rakhaine ☐ Mro ☐ Pangkho ☐ Lusai ☐ Khumi ☐ Chak ☐ Other (specify) _______________________

**Day – 0 Date of visit:** ☐☐-☐☐-☐☐☐☐

1. **Weight:** ☐☐☐.☐ Kg

2. **Temperature:** ☐☐.☐ ˚C

3. **Finger prick (baseline) collected?** ☐ Yes ☐ No

*If yes:* **Blood slide (baseline) collected?** ☐ Yes ☐ No

*If yes:* Time: ☐☐:☐☐ in 24:00 format (e.g. 4pm is 16:00)

**Parasite count (baseline):** ________/500RBC or ___________/200WBC

**Diagnosis:** ☐ Pf ☐ Pv ☐Mixed

*If yes:* **Hemoglobin (baseline) measured?** ☐ Yes ☐ No

*if Yes:* ☐☐.☐ g/dl

4. **Venous blood (baseline) collected?** ☐ Yes ☐

5. **Does this patient have a family history of hemolysis (severe anemia)?** ☐ Yes ☐ No ☐Uncertain

*If yes, was it in response to:*  ☐Medication ☐Food ☐Infection ☐Other

6. **Does this patient have a family history of G6PD deficiency?** ☐ Yes ☐No ☐ Uncertain

7. **Has this patient ever had a blood transfusion?** ☐ Yes ☐ No

*If yes, within the last 12 weeks?* ☐ *Yes* ☐ *No* ☐ *Uncertain*

8. **2^nd^ Blood slide collected?** ☐ Yes ☐ No

*If yes:* Time: ☐☐:☐☐ in 24:00 format (e.g. 4pm is 16:00)

**Parasite count:** ________/500RBC or ___________/200WBC

**Diagnosis:** ☐ Pf ☐ Pv ☐Mixed

9. **Schizontocidal Treatment**

| Schizontocidal treatment | Pf | Pv | mixed |
| --- | --- | --- | --- |
| 1^st^ Dose (observed) | AL given  ☐ Yes ☐ No ☐  Dose:___________ | CQ given  ☐ Yes ☐ No ☐  Dose:___________ | AL given  ☐ Yes ☐ No ☐  Dose:___________ |
| 2^nd^ Dose | AL given  ☐ Yes ☐ No ☐  Dose:___________ | N/A | AL given  ☐ Yes ☐ No ☐  Dose:___________ |
|  | Was this dose given as observed treatment  ☐yes ☐no |  | Was this dose given as observed treatment  ☐yes ☐no |

**Day – 1 Date of visit:** ☐☐-☐☐-☐☐☐☐

10. **Temperature:** ☐☐ **.** ☐˚C

11. **Finger prick collected?** ☐ Yes ☐ No

*If yes:* **Blood slide collected?** ☐ Yes ☐ No

*If yes:* Time: ☐☐:☐☐ in 24:00 format (e.g. 4pm is 16:00)

**Parasite count:** ________/500RBC or ___________/200WBC

*If yes:* **Hemoglobin measured?** ☐ Yes ☐ No

*if Yes:* ☐☐.☐ g/dl

12. **2^nd^ Blood slide collected?** ☐ Yes ☐ No

*If yes:* Time: ☐☐:☐☐ in 24:00 format (e.g. 4pm is 16:00)

**Parasite count :**________/500RBC or ___________/200WBC

13. **Schizontocidal Treatment**

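### The procedures require no second slide on days 0–2 and the CRF has no day 3 page, so the slides needed for falciparum parasite clearance rate and clearance time are not secured

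*Protocol*

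**What the plan says.** Parasite clearance rate in falciparum patients treated with artemether-lumefantrine (AL) is a secondary objective. The Statistical analyses section says "Parasite clearance rate will be defined according to the World Wide Antimalarial Resistance Network guidelines" and defines PCT as the "time elapsed between the patient’s first dose and the time of the first negative blood slide". It gives no sampling times.

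Slide collection is described in four places:

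- **Study Procedures.** A finger prick is taken at enrolment and at each follow-up visit, and visits are daily to day 2.
- **Schedule table.** The microscopy row has one mark on each of days 0, 1 and 2 and an unexplained bracketed mark on day 3. The finger-prick row has no mark on day 3.
- **Microscopy.** "Slides for microscopy will be collected upon enrolment and on all follow up days as well as on any unscheduled visit days". No number per day and no interval is given. Slides from day 0 to day 3 are to be re-read by an expert.
- **CRF (Annex IX).** The item "Blood slide collected" appears twice on each of days 0, 1 and 2. The second occurrence is labelled as a second slide (items 8, 12 and 16), with its own clock time and parasite count. The form goes from day 2 straight to day 6.

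On attendance, Treatment & sample collection says of AL: "The morning dose will be supervised and the patients given tablets for the evening dose".

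**The concern.** A clearance rate is a slope on the log scale, and PCT is read off slide times, so both depend on how many slides are taken and when. The CRF shows that twice-daily sampling was contemplated. No procedure requires it, times it or says which patients it is for. Staff working from the schedule and the text could take one slide a day and be compliant, leaving the second-slide fields empty. Slides never taken cannot be recovered at analysis, so this cannot be left to the statistical analysis plan.

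With one positive count there is no slope. With two there is a slope, but no residual to check it and no way to separate an initial lag from slow decline. Daily slides also put PCT on a roughly 24 h grid. The Background motivates the question by artemisinin resistance elsewhere, and notes that the last systematic Bangladeshi reports came from 2009 studies.

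Day 3 is a second gap. A falciparum patient still positive on day 2 has no scheduled CRF page for a first negative slide until day 9 by the text, or day 12 by the schedule's falciparum row.

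**Working it through.** The protocol states no precision, expected density or clearance speed for this objective, so there is no figure to reproduce.

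**Slides available.** Reading the schedule as one slide per mark gives 3 slides on days 0–2, or 4 with day 3. The CRF has fields for 6 on days 0–2 and none for day 3.

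**Positive counts per patient.** All inputs here are assumptions:

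- Decline: P(t) = P0 × 2^(−t/h), with no lag.
- Detection limit: 1 parasite per 200 WBC (a CRF counting basis) at 8,000 WBC/µL, so L = 8,000/200 = 40/µL.
- P0 = 1,000, 10,000 or 50,000/µL; half-life h = 2, 3, 4, 5 or 6 h.
- Daily slides at 0, 24, 48 and 72 h. With the CRF's second slide, taken as 8 h after the first: 0, 8, 24, 32, 48 and 56 h.

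Examples at P0 = 10,000/µL:

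- h = 3 h: 10,000 × 2^(−8) = 39/µL at 24 h, below 40, so one daily positive.
- h = 5 h: 359/µL at 24 h and 13/µL at 48 h, so two daily positives.

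Each cell shows positives with daily slides → positives with the second slide:

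| P0 (/µL) | h=2 | h=3 | h=4 | h=5 | h=6 |
|---|---|---|---|---|---|
| 1,000 | 1→2 | 1→2 | 1→2 | 1→2 | 2→3 |
| 10,000 | 1→2 | 1→2 | 2→3 | 2→4 | 2→4 |
| 50,000 | 1→2 | 2→3 | 2→4 | 3→5 | 3→6 |

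- Daily: one positive in 4 + 2 + 1 = 7 of 15 cells, two in 1 + 3 + 2 = 6, three in 2. One or two in 7 + 6 = 13 of 15.
- With the second slide: no cell has only one, and at least three occur in 1 + 3 + 4 = 8 of 15.

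**Wider check.** Adding P0 = 5,000 and 100,000/µL and a 6 h lag gives 50 scenarios. Daily slides give one positive in 14 and one or two in 40. With the second slide at 6, 8 or 12 h, at least three positives occur in 36 of 50 at each gap.

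**Clearance time.** True PCT = h × log2(P0/L). At P0 = 10,000/µL, log2(250) = 7.97. Daily slides record 48 h whenever 24 < 7.97h < 48, that is, for h from 24/7.97 = 3.0 to 48/7.97 = 6.0 h. A second slide at 32 h splits this range at 32/7.97 = 4.0 h. At 50,000/µL and h = 3 h, true PCT is 30.9 h, recorded as 48 h with daily slides and 32 h with the second slide.

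**What the second slide does not do.** Take a count error of SD 0.46 on the natural-log scale (an assumption). The slope's standard error is 0.46/√Σ(t − mean t)². Counts at 0 and 24 h give 0.0271 per hour; counts at 0, 8 and 24 h give 0.0266. So where two daily positives already exist, a third adds a check on fit and lag but little precision. Where there is only one, the second makes a slope estimable but imprecise: 0.46/√(4² + 4²) = 0.081 per hour, against a slope of ln 2/3 = 0.231 at h = 3 h.

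**The case against.** The strongest reply is that the protocol never says one slide per day. The schedule marks days, not counts: twice-daily AL also carries a single mark on each of days 0–2. The CRF is an annex of the same protocol and has two timed slides a day. It also asks whether the second AL dose was observed, so a second contact on the same day is contemplated. This stands. A reader might infer that the plan fixes one slide per day. The documents support only that no procedure requires the second slide, and that the text and CRF are unreconciled.

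A reader might also infer that most patients will have too few counts for a slope. That is not supported. Two counts give a slope, and 8 of the 15 cells have at least two with daily slides. The grid is not a patient distribution, and its density, half-life and detection limit are all assumed. One example is on a knife edge: 39/µL against a limit of 40/µL. Slow clearance, the case of most interest, is where daily slides yield more counts. Any stricter minimum under the cited network guideline is not in the documents and is not used here.

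Finally, parasitaemia on days 1, 2 and 3 is already an efficacy endpoint, and early treatment failure and resistance markers also bear on the question. Clearance is therefore one source of evidence, not the study's only signal. This limits what is at stake but does not remove the conflict between the passages.

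**Conclusion.** The point holds as an unreconciled sampling plan for a secondary objective. The mismatch needs no assumptions: the second slide on days 0–2 appears in the CRF but not in the procedures, and the bracketed day 3 slide appears in the schedule but has no CRF page.

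Its size is conditional. If only daily slides are taken, and under the log-linear, no-lag, 40/µL assumptions, one or two positive counts are likely for fast-clearing patients (13 of 15 combinations), and 7 of 15 give no slope at all. PCT is then known only to a 24 h interval, so at 10,000/µL a twofold range of half-lives is recorded as the same value. If the CRF's second slide is taken, these limits ease considerably, though fast clearers still give only two counts. The documents do not show that the clearance objective is unattainable.

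**What to change.** Reconcile Study Procedures, the schedule table, the Microscopy section and the CRF:

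- State the second slide on days 0, 1 and 2 for falciparum and mixed patients, with its target time after the first, as the CRF already provides. Say how it is obtained when the evening dose is taken at home.
- Explain the bracketed day 3 mark and add a day 3 page or slide field to the CRF. The existing day 3 parasitaemia endpoint and the day 3 failure criteria in Annex VII need it in any case.

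The cost is wording, one CRF field, and up to three more finger-prick slides per patient. At the target of about 160 falciparum patients that is at most 3 × 160 = 480 slides, plus those from mixed infections, with the added attendance and re-reading.

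If only daily slides are feasible, remove the second-slide items from the CRF, rely on the existing endpoint of parasitaemia on days 1, 2 and 3 in place of a clearance rate, and analyse PCT as interval-censored. That costs wording and the day 3 field only. Either choice should be made before enrolment.

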**Table: Maximum amount of venous blood collected on d0 / body weight**

| **Patient’s approximate weight in kilograms** | **Amount (mL)** |
| --- | --- |
| >6 to 7 | 4-5 |
| >7 | 5 |

All participants will be followed daily until day 2 to provide supervised treatment and ensure clinical and parasitological recovery following chloroquine (Pv arm) or artemether-lumefantrine (Pf arm and Pf/Pv arm) treatment.

Thereafter patients (excluding those with severe G6PD deficiency) will be given unsupervised primaquine for 1 dose (Pf arm) or 14 doses (Pv/mix arm) and reviewed again after 7 days (day 9), 14 days (day 16), 21 days (day 23) and 28 days (day 30). All P. vivax and mixed infections will in addition be followed up after 3 and 10 days (day 6 and 12 respectively) to assure the safety of the provided treatment. Any patient developing signs and symptoms indicative of a malarial episode or an adverse event within the follow up period will be asked to re-attend the clinic for an unscheduled visit, where they will be offered clinical management according to local clinic guidelines. A fingerprick will be performed during every follow up and unscheduled visit, 5ml of blood will be collected for every recurring malaria episode (see table below). Information on adverse events will be collected during every visit. Whenever possible a pill count will be performed on day 16.

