## Efficacy endpoints

- Proportion of patients with any parasitemia on day 1, 2 and 3 after treatment
- Proportion of patients with fever on day 1, 2 and 3 after treatment
- Recurrence of parasitaemia within 30 days of follow up
- Proportion of Pf patients with gametocytemia on any of the follow up dates.

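### Parasite clearance time stops at the first negative slide, with no requirement to stay negative and no allowance for the gap between slides

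*Protocol*

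**What the plan says.** The protocol's Statistical analyses section describes two measures of clearance. On the first it says: "Parasite clearance rate will be defined according to the World Wide Antimalarial Resistance Network guidelines". The second, PCT, runs from the first dose to "the time of the first negative blood slide". It asks for no second negative slide, gives no rule for the time between slides and names no summary statistic for PCT.

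The Efficacy endpoints section lists "Proportion of patients with any parasitemia on day 1, 2 and 3 after treatment". PCT is not on that list, nor among the synopsis endpoints.

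The places that determine when slides exist for falciparum patients do not agree:

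- **Study Procedures:** "All participants will be followed daily until day 2". The next review named for all arms is day 9.
- **Treatment & sample collection, falciparum paragraph:** "All patients will be asked to return for follow up on day 9, day 16, day 23, day 30". No day 3 visit is named.
- **Schedule table:** the falciparum follow-up row marks days 0, 1 and 2, has a bracketed day 3, and then goes to day 12 with no mark on day 9. The microscopy row also brackets day 3, and the bracket is not explained. The finger-prick row is blank on day 3.
- **Microscopy section and Annex VII:** both presuppose a day 3 slide, the first for expert re-reading and the second for early treatment failure.
- **Case record form (Annex IX):** day 2 is followed by day 6, with no day 3 page. A second timed slide can be recorded on days 0, 1 and 2.

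**The concern.** The definition uses the clock time of one slide as if it were the time of clearance. This can go wrong in two directions. A patient with an intermittent negative slide is given a time that is too short and that conflicts with the same patient's entry in the daily parasitaemia proportions. A patient who clears after the last daily slide is given the time of the next visit, however far off that is.

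The second error falls on slow clearers. These are the patients of most interest in a study whose background section raises artemisinin resistance and notes how old the last systematic Bangladeshi reports are. A long PCT could then be read as delayed clearance when it only reflects when the patient was next seen.

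**Working it through.** The protocol states no PCT figure, so there is none to reproduce. The check applies the definition to the visit days, taking first dose as 0 h and each slide at 24 h × day.

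**1. Intermittent negative.** Slides: day 1 negative, day 2 positive, next slide negative. The literal PCT is 24 × 1 = 24 h. Under the day 2 efficacy endpoint the same patient is parasitaemic at 48 h.

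As an illustration, assume that each slide from a patient who is still parasitaemic reads negative with probability s, independently, with s from 2% to 10%. Over two such slides:
- at least one negative: 1 − (1 − s)² = 4.0% to 19.0%
- both negative: s² = 0.04% to 1.0%

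These are shares of patients still parasitaemic at both slides. They show why requiring sustained negativity matters; s itself is not in the documents.

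**2. Last positive slide on day 2, next slide negative (falciparum).** A positive day 2 slide is not in itself early failure under Annex VII, which requires a day 2 count above day 0 or danger signs, so such patients stay in follow-up.

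| Next slide | Source | Literal PCT | What the data show | Width |
| --- | --- | --- | --- | --- |
| Day 3 | bracketed entry in the schedule table | 3 × 24 = 72 h | 48 to 72 h | 24 h |
| Day 9 | follow-up text | 9 × 24 = 216 h | 48 to 216 h | 168 h |
| Day 12 | falciparum row of the schedule table | 12 × 24 = 288 h | 48 to 288 h | 240 h |

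The day 9 figure agrees with the text's own count: day 2 + 7 = day 9.

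**3. Effect on a mean, if one were reported.** Each 1% of patients given 216 h instead of 72 h adds 0.01 × (216 − 72) = 1.44 h. For 288 h the addition is 0.01 × (288 − 72) = 2.16 h.

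With the 160 falciparum patients of the Sample Size section, and assuming that all others average 36 h, the mean is (1 − f) × 36 + f × next-slide time:

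| Share f positive on day 2 | Patients | Day 3 | Day 9 | Day 12 |
| --- | --- | --- | --- | --- |
| 5% | 8 | 37.8 h | 45.0 h | 48.6 h |
| 10% | 16 | 39.6 h | 54.0 h | 61.2 h |

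The shares and the 36 h are assumptions.

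**4. Effect on a median.** If fewer than half are positive at 48 h, more than half have a literal PCT of 48 h or less. Changing the later values from 72 to 216 or 288 h leaves the median where it was.

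**The case against.** The strongest reply is that a day 3 slide is plainly intended. The schedule table brackets it, the Microscopy section re-reads it, an efficacy endpoint uses it and Annex VII depends on it. With it, the assigned time is 72 h and the uncertainty is one day. This stands as far as it goes. A reader might infer that any falciparum patient positive on day 2 will be given 216 h; the documents do not support that, because 216 h is one of three possible values. But neither the follow-up text nor the case record form secures the slide.

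A second reply is that little rests on PCT. The secondary objective concerns the clearance rate, which is defined separately through the network guidelines, and PCT is not a listed endpoint. No mean of PCT is planned: the list of summary statistics in the same section concerns vital signs in the safety data. This also stands. A reader might infer that the clearance objective itself is distorted, or that an inflated mean will be reported. Neither follows from the text.

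Third, there are safeguards: optional second slides on days 0 to 2, slides at unscheduled visits, and expert re-reading with a third reader for discordant results. These help in part. Second slides do not reach past day 2, unscheduled visits depend on symptoms, and re-reading removes misread slides but not true intermittent negatives.

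Finally, a choice of summary can be left to an analysis plan. The definition, however, is fixed in the protocol itself.

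**Conclusion.** The point holds in a limited form. The stated rule gives a wrong event time for a patient with an intermittent negative (24 h for someone parasitaemic at 48 h). It also lets the visit calendar set the value for a falciparum patient last positive on day 2 (72, 216 or 288 h). That part needs only the definition, the visit days and slides at 24-h multiples.

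The effect on any summary is conditional. A mean would rise by about 1.4 h per 1% of patients moved from 72 to 216 h. A median would not respond to the gap while fewer than half are positive at 48 h. How many patients will be positive on day 2, and whether each will have a day 3 slide, cannot be told from the protocol. The 288 h value rests on the falciparum row of the schedule table as it reads in the text copy used here.

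**What to change.** - Define clearance as the first negative slide that is not followed by a positive one at the next scheduled visit.
- Treat PCT as interval-censored between the last positive slide and that negative slide. Summarise it by an interval-censored median, beside the day 1, 2 and 3 parasitaemia proportions already planned.
- Reconcile Study Procedures, Treatment & sample collection, the schedule table and the case record form on two matters: whether a day 3 slide is taken and recorded, and whether day 9 or day 12 applies to falciparum patients.

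The first two changes are analysis wording and use slides already collected. The cost is that PCT is reported as an interval-based median, not as a single time per patient. Interval censoring states the uncertainty honestly but does not narrow it: without a day 3 slide the interval stays 168 or 240 h wide. Where the confirming slide falls a week or more later, a positive result there could also be a recurrence, so the rule should say how that case is classed.
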